## Abstract

**Background:**

Head and neck cancers (HNCs) are among the most common malignancies, which often require multimodal treatment that includes radiation therapy and chemotherapy. Patients with HNC have a high burden of symptoms due to both the damaging effects of the tumor and the aggressive multimodal treatment. Close symptom monitoring over the course of the disease may help to identify patients in need of medical interventions.

**Objective:**

This APCOT (App-Controlled Treatment Monitoring and Support for Head and Neck Cancer Patients) trial is designed to assess the feasibility of monitoring HNC patients during the course of (chemo)radiation therapy daily using a mobile app. Additionally, symptom patterns, patient satisfaction, and quality of life will be measured in app-monitored patients in comparison to a patient cohort receiving standard-of-care physician appointments, and health economy aspects of app monitoring will be analyzed.

**Methods:**

This prospective randomized single-center trial will evaluate the feasibility of integrating electronic patient-reported outcome measures (ePROMs) into the treatment workflow of HNC patients. Patients undergoing definitive or adjuvant (chemo)radiation therapy as part of their HNC treatment at the Department of Radiation Oncology, University Medical Center Freiburg (Freiburg, Germany) will receive weekly physician appointments and additional appointments as requested to monitor and potentially treat symptoms during the course of treatment. Patients in the experimental arm will additionally be monitored daily using a dedicated app regarding their disease- and treatment-related symptoms, quality of life, and need for personal physician appointments. The feasibility of ePROM monitoring will be tested as the primary endpoint and will be defined if ≥80% of enrolled patients have answered ≥80% of their daily app-based questions. Quality of life will be assessed using the validated European Organisation for Research and Treatment of Cancer questionnaires, and patient satisfaction will be measured by the validated Patient Satisfaction Questionnaire Short Form at the initiation, in the middle, and at completion of radiation therapy, as well as at follow-up examinations. Additionally, the number and duration of physician appointments during the course of radiation therapy will be quantified for both ePROM-monitored and standard-of-care patients.

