### Statistical Analysis

The sample size was calculated based on the primary endpoint using the exact binomial test. For this trial, we defined feasibility as the ability of ≥80% of trial patients to answer ≥80% of mobile ePROM questions during the course of (chemo)radiation therapy. With an assumed percentage of 89% for the primary endpoint, a sample size of 50 patients in the experimental arm provides a power of 80% (1 – β) to a one-sided significance level of 5% (α). Power calculations were carried out using G*Power software version 3.1.9.2 (University of Düsseldorf, Germany).

Descriptive statistics will be used to analyze the secondary endpoints, including mean (SD) as well as median (IQR) for continuous variables, and absolute and relative numbers for categorical variables. Multivariate regression models will be employed to assess potential correlations between clinical parameters and data collected for the primary and secondary endpoints. The control group will be included in the analysis, and the randomization of each patient will be considered as a variable. Sum scores will be derived from the quality of life and patient satisfaction questionnaires, and will be compared between study arms using Mann-Whitney *U* tests.

To investigate the association between patient-reported outcomes and the necessity for inpatient treatment, a chi-square test will be employed.

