### Limitations and Future Perspectives

This trial involves a mobile app used by patients via an investigator-provided tablet computer, and the acquired data will be integrated into the institutional clinical trial databases according to the required data protection and data security regulations. It is conceivable that a dedicated app on patients’ private devices would have logistic advantages and enable patients to report outcome parameters independently from the treatment time and from outside as well. However, we felt that utilizing patient-owned devices for reporting may introduce a selection bias, as this approach would exclude patients who do not own a mobile device, especially elderly patients [14]. By using investigator-provided tablet computers, all HNC patients, irrespective of age or technical abilities, can be included in this trial. Additionally, avoidance of data transmission outside the hospital network complies with current national data protection standards.

As each cycle of ePROM collection is carried out over 5 days, it is possible that symptom reporting may be delayed for up to 4 days before items are repeated. However, in case of new symptoms, all patients in the experimental arm have the ability to request physician appointments daily via the app if deemed necessary. The frequency of ePROM assessment corresponds well with current national and international standards of weekly physician appointments during radiotherapy.

Once feasibility has been demonstrated for HNC patients using institutional devices, the range of the app will be expanded in a future trial to patients’ personal devices so as to uncouple reporting from the hospital visits.

To date, there is no consensus on how feasibility for app-based treatment monitoring is defined and can be tested. We therefore chose a feasibility endpoint for this trial based on clinical experience. Two previously published large surveys suggest that more than 75% of patients would be willing to report ePROMs as part of treatment monitoring during radiation therapy [10,15]. Therefore, patient adherence of ≥80% is within the estimations of these surveys and seems to be a realistic assumption to prove feasibility.

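### The primary endpoint has an observed-80% success rule and a one-sided exact test with no stated null; the two disagree on some results, and nothing says which decides

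*Protocol article*

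**What the plan says.** The abstract (Methods) says two things about the primary endpoint in one sentence. Feasibility is to be tested: "The feasibility of ePROM monitoring will be tested as the primary endpoint". It also "will be defined if ≥80% of enrolled patients have answered ≥80% of their daily app-based questions". The second statement describes a result already obtained, so it reads as a cut-off on the observed proportion.

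The Statistical Analysis section repeats the threshold: "we defined feasibility as the ability of ≥80% of trial patients to answer ≥80% of mobile ePROM questions". On the design it says: "The sample size was calculated based on the primary endpoint using the exact binomial test". The design inputs are "With an assumed percentage of 89% for the primary endpoint" and "a sample size of 50 patients in the experimental arm", with 80% power at a one-sided 5% level. It gives no null proportion and no number of patients at which the test succeeds.

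Limitations and Future Perspectives cites two surveys in which more than 75% of patients were willing to report, and concludes that "patient adherence of ≥80% is within the estimations of these surveys and seems to be a realistic assumption to prove feasibility".

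**The concern.** A success rule based on the observed proportion and a significance test are different decisions. To show at 5% that a true rate exceeds some value, the observed rate must lie clearly above that value. An observed rate of exactly 80% cannot do this against 80%, and in 50 patients it cannot do it against 75% either.

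Feasibility is the only primary endpoint, and the Discussion makes the planned move to patients' own devices depend on it. If a result meets one rule and not the other, the conclusion could be chosen after the data are known. The quoted 5% error rate would then not describe the decision actually taken.

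**Working it through.** **Inputs.** From Statistical Analysis: n = 50 in the app arm, assumed rate 89%, one-sided alpha 5%, stated power 80%. From the definition of feasibility: observed proportion at least 80%, so 0.80 × 50 = 40 patients. The null proportion p0 is not in the document. I treat it as an assumption and examine 70% to 80%; 80% is the feasibility threshold, and 75% is the only other benchmark in the text.

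**Formulas.** With X ~ Binomial(50, p), the critical count r is the smallest r with P(X ≥ r | p0) ≤ 0.05. Power is P(X ≥ r | 0.89). A result from 40 to r − 1 meets the observed rule but fails the test; its probability at 89% is P(X ≥ 40 | 0.89) − P(X ≥ r | 0.89), where P(X ≥ 40 | 0.89) = 0.982.

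**Step 1: the plan's own power.**

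| Assumed null | P(X ≥ r − 1) under the null | Critical count r | P(X ≥ r) under the null | Power at 89% |
|---|---|---|---|---|
| 70% | 0.079 | 41 | 0.040 | 95.7% |
| 75% | 0.092 | 43 | 0.045 | 82.1% |
| 76% | 0.062 | 44 | 0.028 | 69.1% |
| 80% | 0.103 | 45 | 0.048 | 52.4% |

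With a null of 80%, the stated 80% power is not reproduced. Approximations do not rescue it: the normal approximation gives 47.3% and the arcsine 55.2%. The smallest sample with at least 80% power would be 106 (critical count 92, power 81.4%). With a null of 75%, 50 is the smallest sample that reaches 80% power. Nulls of 73% and 74% also give r = 43 and 82.1% power at n = 50, but fewer than 50 patients would already reach 80% power there (41 and 43).

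**Step 2: where the rules disagree.**

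- Null 80%: 40 to 44 of 50. Probability at 89%: 0.982 − 0.524 = 0.458. At a true 80% it is 0.584 − 0.048 = 0.536.
- Null 75%: 40 to 42 of 50. Probability at 89%: 0.982 − 0.821 = 0.161.
- Null 70%: 40 of 50 only. Probability at 89%: 0.982 − 0.957 = 0.025.

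The critical count is never 40 in this range, so some conflict always remains.

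**Step 3: error of the observed rule if it decides alone.**

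| True rate | P(X ≥ 40) | P(X ≥ 43) | P(X ≥ 45) |
|---|---|---|---|
| 75% | 26.2% | 4.5% | 0.7% |
| 80% | 58.4% | 19.0% | 4.8% |
| 89% | 98.2% | 82.1% | 52.4% |

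**Step 4: what the data would support.** One-sided 95% Clopper-Pearson lower bounds are 68.4% for 40/50, 75.3% for 43/50, 77.7% for 44/50 and 80.1% for 45/50.

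**The case against.** The strongest reply is that there is only one rule. The abstract says feasibility will be tested, and the definition in Statistical Analysis can be read as a target for the true rate, with the exact test as the means of judging it. The exact test is named only for the sample size, the Discussion calls 80% an assumption and not a criterion, and a condensed article may leave the critical count to a fuller document. Part of this stands: the missing count alone would not be a finding. But the abstract's wording describes an observed result, and the printed power statement does not fit a test of the 80% threshold. The text therefore does not settle which rule is meant.

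A reader might infer that the plan tests against 80%, that 40 to 44 of 50 is simply the conflict zone, and that a bar of 45/50 is already implied. The document does not support this. It names no null, and its own sample size and power speak against 80%. Under a null of 75%, results of 43 and 44 pass both rules.

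A reader might also infer from the words about enrolled patients that the proportion cannot exceed 50%, because controls have no app. The abstract confines the app to the experimental arm and the power statement names 50 patients in that arm, so this is only loose wording.

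**Conclusion.** The point holds in this form: the plan prints an observed-80% success rule beside a one-sided 5% exact test whose null is unstated, and does not say which decides. This does not depend on choosing a null, because the rules disagree on at least one result for every null checked from 70% to 80%.

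The size does depend on it. With a null of 80%, the ambiguous results are 40 to 44 of 50, and the power claim is also wrong. With a null of 75%, they are 40 to 42 and the power claim is right. That 75% was intended is an inference from the fit to the sample size and from the survey figure; the document does not say so. Under either null, the 5% level does not apply to the observed rule.

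The calculations assume that all 50 app-arm patients are counted and are independent.

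**What to change.** Before any completion data are seen, state the null (unacceptable) rate, make the exact test the single deciding rule, and give its critical count everywhere feasibility is defined. Two versions are consistent with n = 50:

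- **Null 75%:** feasibility is concluded if at least 43 of the 50 patients randomised to the experimental arm meet the 80% completion criterion. The stated power stands (82%). The conclusion is only that the true rate exceeds 75%; at a true 80% this rule succeeds 19.0% of the time.
- **Null 80%:** feasibility is concluded if at least 45 of those 50 meet the criterion. The stated power must be corrected to about 52% at 89%.

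In both versions, report the observed proportion with its exact confidence interval, and replace the references to enrolled patients and trial patients with patients randomised to the experimental arm.

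The cost is a few sentences and no extra enrolment. What the sponsor gives up is either the claim to have shown 80% or the claim to 80% power; with 50 patients and an assumed 89%, both cannot be kept.

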**Results:**

This trial will enroll 100 patients who will be randomized (1:1) between the experimental arm with ePROM monitoring and the control arm with standard patient care. Recruitment will take 18 months, and trial completion is planned at 24 months after enrollment of the last patient.

**Conclusions:**

This trial will establish the feasibility of close ePROM monitoring of HNC patients undergoing (chemo)radiation therapy. The results can form the basis for further trials investigating potential clinical benefits of detailed symptom monitoring and patient-centered care in HNC patients regarding oncologic outcomes and quality of life.

**Trial Registration:**

German Clinical Trials Register DRKS00020491; https://www.drks.de/drks_web/navigate.do?navigationId=trial.HTML&TRIAL_ID=DRKS00020491

**International Registered Report Identifier (IRRID):**

PRR1-10.2196/21693

## Introduction

Head and neck carcinomas (HNCs) are among the most common malignancies worldwide with more than 600,000 new diagnoses and 400,000 deaths annually [1]. Disease-associated morbidities are widespread in HNC patients and can affect the ability to breathe or swallow, often requiring life-saving placements of tracheostomy or gastrostomy tubes [2-4]. For nonmetastatic HNCs, multimodal treatment comprises surgery and radiation therapy, and locally advanced cancers often require a combination of radiation therapy and concomitant chemotherapy [5,6]. The treatment itself can result in severe acute and long-lasting toxicities that may significantly impact patients’ quality of life and require medical interventions [7].

Usually, treatment-related acute toxicities are assessed several times during the course of (chemo)radiation therapy and in increasing intervals during the follow-up period by medical professionals. However, there are several downsides to physician-assessed outcome measures for HNC patients. There are increasing gaps between appointments, during which no assessment is possible and patients may get lost to follow up; additionally, patients may not report the entirety of their symptoms during timed interactions with their health care provider [8,9]. In this respect, mobile apps may help to bridge the gap between appointments, and may provide a low-threshold tool to regularly and frequently report disease-related and treatment-related symptoms and outcomes. Previous surveys have demonstrated high acceptance levels for the usage of patient monitoring apps both for health care providers and cancer patients [10,11]. Additionally, two randomized controlled trials have been published that demonstrated a survival benefit of telemonitoring for patients with nonsmall cell lung cancers and metastatic cancers compared to the standard of care, likely due to an earlier initiation of salvage treatments in cases of recurrence symptoms [12,13].

HNC patients may especially benefit from app-based electronic patient-reported outcome measures (ePROM) monitoring, as frequent symptom control may not only help to detect recurrences earlier but could also help to assess the dynamics of treatment-related toxicities, thereby enabling faster medical interventions. In this respect, both patient outcomes and quality of life may potentially be improved. However, the compliance and acceptance levels of HNC patients toward an app-based ePROM monitoring system remain to be demonstrated. The aim of this trial, APCOT (App-Controlled Treatment Monitoring and Support for Head and Neck Cancer Patients), is to assess the feasibility of ePROM monitoring and support for HNC patients, as well as to measure global and disease-related quality of life, patient satisfaction, and economic aspects.

## Methods

### Study Design

This trial is designed as a single-center prospective randomized controlled trial and will be carried out at the Department of Radiation Oncology, University of Freiburg Medical Center in Freiburg, Germany. Patients with histologically proven HNCs scheduled for (chemo)radiation therapy will receive weekly physician appointments and additional appointments if medically indicated in both trial arms to monitor and potentially treat symptoms occurring during the course of treatment (standard of care). Patients in the experimental arm will additionally receive daily ePROM monitoring during (chemo)radiation. Patient-reported outcomes regarding symptom control as well as general and disease-specific quality of life will be monitored daily by a mobile app in the experimental arm that is provided to the patients on a tablet computer. All patients in the experimental arm will have the ability to request a physician appointment if necessary on a daily basis via the app. The frequency and total duration of consultations will be quantified, and the necessity and duration of inpatient care will be assessed if necessary during the course of treatment. Routine blood test results and clinical data from the patient files, including physician-reported outcomes, will be analyzed to find potential correlations with the ePROMs and to assess potential predictive factors necessitating intensified medical care.

### Patient Recruitment

All patients with HNCs are screened for their eligibility to participate in this trial by a study nurse prior to the initiation of (chemo)radiation therapy; the treating physician then informs potential patients about the details of the trial and answers potential questions. If (chemo)radiation therapy is medically warranted and patients provide written informed consent to participate, they are randomized between the standard-of-care monitoring and ePROM monitoring arms during the course of treatment. Block randomization with a variable block length will be used to allocate patients to the study arms.

According to institutional patient statistics, approximately 300 eligible patients are treated annually in our department. The recruitment period is set at 18 months to recruit 50 patients to each study arm, assuming a participation rate of 20%. The study duration for each patient varies according to the treatment concept, and the average time from enrollment in the trial to the first follow up ranges from 12 to 14 weeks. Figure 1 provides a detailed timeline for the individual trial steps and assessments. The SPIRIT (Standard Protocol Items: Recommendations for Interventional Trials) flowchart is presented in Multimedia Appendix 1.

**Figure 1 figure1:**
[figure not shown]
Flow chart outlining the study design and the timeline for the individual trial endpoints. HNC: head and neck cancer; VAS: visual analog scale; EORTC: European Organisation for Research and Treatment of Cancer; PSQ-18: Patient Satisfaction Questionnaire Short Form.

### Inclusion and Exclusion Criteria

To participate in this trial, patients must fulfill the following inclusion criteria: (1) histologically confirmed tumor in the head and neck region, (2) indication for chemoradiation or radiation therapy, (3) aged ≥18 years, (4) Karnofsky performance score ≥50%, and (5) provision of written informed consent.

The following criteria will exclude patients from participating in this trial: (1) significant neurological or psychiatric diseases and (2) inability to give informed consent.

### ePROM Monitoring During Treatment and Support

Patients that are randomized to the experimental arm will be provided with a mobile app on a tablet computer prior to each radiation treatment fraction and will be asked to answer 7-8 questions. The app will be provided by ONCARE GmbH (Munich, Germany) and will be run on an Android system. An introductory session with a study nurse will be scheduled for each patient in the experimental arm to familiarize them with the tablet and the app. If requested, this introductory session can be repeated once. The answers will be collected and documented as patient-reported outcomes. Questions will be taken from the validated H&N35 quality of life questionnaire developed by the European Organisation for Research and Treatment of Cancer (EORTC). The questions cover overall and treatment-related well-being as well as specific symptoms, and the 35 questions of the EORTC module will be rotated so that each patient is presented with each question once weekly. As the respective questionnaires have been validated in multiple languages, the monitoring app will be multilingual. After completing the daily EORTC questions, patients will be asked about their need to consult a physician on each treatment day. If they require a physician appointment, the radiation technologist is informed by an automatic notification system prior to applying the daily treatment and will schedule a consultation with the treating physician on that day. Each patient in the experimental study arm will be seen by the treating physician for routine checkups weekly in addition to the visits requested through the app. The total number and duration of all physician appointments will be measured and documented.

Patients in the standard-of-care arm will receive routine weekly physician appointments during the course of treatment and can request additional consultations through the treating radiation technologist as per institutional standards. Patients in both study arms will also receive weekly blood tests. As the standard-of-care physician appointments are also part of the experimental arm, the mobile therapy monitoring provides an additional individualized method of care during (chemo)radiation therapy.

A sample screenshot of the mobile app is shown in Figure 2.

**Figure 2 figure2:**
[figure not shown]
Sample screenshot of the mobile app used for patient monitoring during radiation therapy.

### Primary and Secondary Endpoints

This trial aims to test the feasibility of an ePROM-based treatment monitoring and support system for HNC patients as the primary endpoint. The trial will measure the percentage of patients answering ≥80% of ePROM questionnaires during the course of (chemo)radiation therapy, and the number of answered questions for each treatment day will be documented for every patient to assess feasibility. Feasibility in this trial is defined based on clinical and logistical considerations. We assume that due to logistic constraints unrelated to this trial, patients will not receive ePROM questionnaires for a certain percentage of treatment fractions (eg, due to personnel changes, technical outages, postponement of treatment fractions). Based on clinical experience from preliminary tests, we assume that the proportion of irregularities during routine patient treatment will amount to approximately 20%.

The following secondary endpoints will also be measured: patient satisfaction, health-related quality of life, number and duration of physician appointments, number of days spent as an inpatient for treatment-related toxicities, and cost aspects. Patient satisfaction will be measured by a 10-step visual analog scale and the validated Patient Satisfaction Questionnaire Short Form (PSQ-18) questionnaire that tests 18 items in 7 subscales using a Likert scale ranging from 1 to 5. A total sum score will be calculated from the PSQ-18 questionnaire and will be transformed to a 5-point scale. Health-related quality of life for patients in both study arms will be measured using the validated EORTC QLQ-C30 questionnaire.

Patients will be asked to answer questionnaires before the initiation of (chemo)radiation therapy, in the middle (usually week 4), and upon completion of treatment (Figure 1). Additionally, patients will be presented with the questionnaires at follow-up visits.

The number of all physician appointments will be documented, and the duration of individual appointments will be measured to estimate cost factors for ePROM monitoring during treatment. The beginning and completion of physician appointments are routinely marked by status flags by the physician within the hospital’s radiation oncology information system (MOSAIQ, Elekta, Stockholm, Sweden), and the duration of each individual consultation can therefore be extracted from the system. A randomized design was chosen for this trial to assess the completeness of acquired data between both arms and to compare the two groups regarding the secondary endpoints.

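### If undelivered questionnaires count against the patient, as the stated rationale implies, the expected 20% loss, the 80% per-patient bar and the assumed 89% pass rate do not fit together

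*Protocol article*

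**What the plan says.** All places are in the Methods of the protocol article unless stated otherwise.

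- **Expected loss (Primary and Secondary Endpoints).** Feasibility is said to rest on clinical and logistical considerations. For reasons unrelated to the trial, "patients will not receive ePROM questionnaires for a certain percentage of treatment fractions", and "we assume that the proportion of irregularities during routine patient treatment will amount to approximately 20" percent. Staff changes, technical outages and postponed fractions are given as examples.
- **Per-patient bar (same section).** The trial measures the "percentage of patients answering ≥80% of ePROM questionnaires during the course of (chemo)radiation therapy".
- **Trial-level criterion (Statistical Analysis).** Feasibility is "the ability of ≥80% of trial patients to answer ≥80% of mobile ePROM questions". The abstract also counts questions.
- **Planning assumption (Statistical Analysis).** "With an assumed percentage of 89% for the primary endpoint", "a sample size of 50 patients in the experimental arm provides a power of 80" percent, using an exact binomial test at a one-sided 5% level.

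Nowhere does the article say whether a questionnaire that was never offered stays in the denominator. It does not derive the 89%, and it makes no allowance for patient non-response on top of the 20%.

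**The concern.** The only stated reason for an 80% per-patient bar is that about 20% of fractions will have no questionnaire. That reasoning makes sense only if those fractions count against the patient. But then the expected score of a perfectly adherent patient sits on the bar itself, and chance alone puts roughly half of such patients below it. An 89% pass rate is not compatible with that.

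What is at stake is the meaning of the primary result. The introduction names patients' compliance and acceptance as the open question. On the all-fractions reading, a failed endpoint could reflect staffing and outages instead. With the denominator left open, a choice made after the data are in could reverse the conclusion.

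A smaller gap lies in the same definition: one section counts questionnaires, while the abstract and the statistical section count questions. With 8 questions a day, a patient who answers 6 of them every day scores 6/8 = 75% and fails on questions, but might pass on questionnaires.

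**Working it through.** **Inputs.** From the article: expected loss 20%; per-patient bar 80%; null proportion 0.80; assumed proportion 0.89; n = 50; one-sided alpha 0.05; one tablet session per fraction. Assumed: F = 30–35 fractions per patient. The article gives no number, but mid-treatment is usually week 4 and a question cycle takes 5 days.

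**1. The plan's own test.** Let Y ~ Binomial(50, p) be the number of patients who pass. P(Y ≥ 44 | 0.80) = 0.103 and P(Y ≥ 45 | 0.80) = 0.048, so the test needs 45 of 50. Power at p = 0.89 is P(Y ≥ 45 | 0.89) = 0.524, so the stated 80% does not reproduce from these inputs. That is a separate matter, and nothing below depends on it.

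**2. Pass probability for a fully adherent patient, all fractions in the denominator.** Let X ~ Binomial(F, 0.80) be the number of fractions with an answered questionnaire. The patient passes if X ≥ 0.8F, rounded up.

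| F | Needed | P(pass) |
|---|---|---|
| 30 | 24 | 0.607 |
| 31 | 25 | 0.571 |
| 32 | 26 | 0.535 |
| 33 | 27 | 0.500 |
| 34 | 28 | 0.466 |
| 35 | 28 | 0.599 |

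The movement between rows comes from rounding up. The range is 47–61%.

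**3. Losses clustered within patients.** Beta-binomial with mean 0.80 and within-patient correlation ρ, a = 0.8(1/ρ − 1), b = 0.2(1/ρ − 1). For ρ from 0.01 to 0.30 and F = 30, 33 and 35, P(pass) runs from 0.511 to 0.650.

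**4. Consequence for the trial.**

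| True pass rate | P(Y ≥ 45) | P(Y ≥ 40) |
|---|---|---|
| 0.50 | below 0.000001% | 0.001% |
| 0.60 | 0.0003% | 0.22% |
| 0.629 | 0.0016% | 0.73% |
| 0.65 | 0.005% | 1.6% |

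**5. What 89% would require.** Solving P(X ≥ 0.8F) = 0.89 for the share of all fractions answered gives 0.862 (F = 30), 0.875 (F = 33) and 0.859 (F = 35). That is a total loss, logistic and patient together, of about 12.5–14%.

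**6. Sensitivity to the loss, perfect adherence, F = 30, 33 and 35.**

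| Loss | P(pass) |
|---|---|
| 20% | 0.50–0.61 |
| 15% | 0.78–0.86 |
| 14% | 0.83–0.89 |
| 12.5% | 0.89–0.94 |

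In the other direction, a 20% loss with 95% of offered questionnaires answered gives 0.8 × 0.95 = 0.76 of fractions answered, and P(pass) of 0.29–0.40.

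**7. Undelivered questionnaires excluded.** A fully adherent patient scores 100%. Nothing then conflicts with 89%, but the 20% gives no reason to set the bar at 80%.

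**The case against.** A reader might infer that the trial is almost certain to fail however well patients adhere. The document does not support that without conditions, for three reasons.

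- **The denominator is not written down.** The abstract speaks of the patient's own daily questions in the app, which can mean questions actually presented. On that reading there is no clash with 89%. A condensed article may also leave the exact definition to the full protocol. This stands, and it is why the point is conditional. It does not remove the point, because the article itself offers the 20% as grounds for its feasibility definition, and on the second reading those grounds fall away.
- **The 20% may overstate lost questionnaires.** It describes irregularities, and postponement is one example. The tablet is offered before each fraction, so a postponed fraction given later may bring its questionnaire with it. The pass rate is steep in this input (step 6). This also stands, although the article lists postponement among the reasons for not receiving a questionnaire and gives 20% as the expected amount, not a ceiling.
- **Counting logistics may be deliberate.** The abstract's aim is to integrate reporting into the treatment workflow, and an endpoint that includes tablet delivery serves it. That is a legitimate choice, but the three figures would then have to agree on that basis.

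The discussion does cite surveys in which more than 75% of patients would be willing to report. That concerns the share of willing patients. It supports neither an 80% bar within a patient nor the 89%.

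The difference between questionnaires and questions is minor by itself, since answered questions are to be documented for each treatment day anyway.

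**Conclusion.** The concern holds in conditional form. With all fractions in the denominator, the 20%, the 80% and the 89% cannot all stand: about 47–61% of fully adherent patients would pass, or 51–65% with clustering, and the chance of 45 of 50 is about 0.005% or less. With undelivered questionnaires excluded, the 89% is possible but the 80% bar loses its stated basis. Either way the passages need reconciling.

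The figures rest on 30–35 fractions (assumed), a mean loss of 20% that is truly lost, and every offered questionnaire answered. The exact percentages move with these assumptions. What does not depend on the fraction count is that a mean placed at the threshold leaves roughly half of patients below it.

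This should be fixed. It is a matter of definition that can be settled cheaply, and it does not show that the trial must fail.

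**What to change.** - **One unit.** Count questions throughout the abstract, the endpoint section and the statistical section.
- **One denominator.** Define the primary variable per patient as questions answered divided by questions due on delivered fractions at which the tablet was offered. Fractions after a patient declines or stops using the app while still on treatment count as unanswered.
- **Controlled exclusions.** Leave out only fractions with a non-delivery reason logged at the time. Staff know the allocation, so reasons assigned later would be open to influence.
- **Logistics on its own line.** Report the share of delivered fractions at which the tablet was offered as a separate logistic-feasibility figure, and give the all-fractions version as a sensitivity analysis.
- **New basis for the figures.** Restate why the bar is 80% and why 89% is expected on this denominator, since the 20% no longer serves.

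If the sponsor prefers to keep all fractions in the denominator, the article should say so and reconcile the 20%, the 80% and the 89% instead.

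The cost is revised wording and a reason code for each missed tablet. The downside is that logistic feasibility is judged separately and no longer inside the primary endpoint.
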